## Abstract

**Background:**

Respiratory viruses are associated with a huge socio-economic burden and are responsible for a large proportion of acute respiratory illness in hospitalised adults. Laboratory PCR is accurate but takes at least 24 h to generate a result to clinicians and antigen-based point-of-care tests (POCT) lack sensitivity. Rapid molecular platforms, such as the FilmArray Respiratory Panel, have equivalent diagnostic accuracy to laboratory PCR and can generate a result in 1 h making them deployable as POCT. Molecular point-of-care testing for respiratory viruses in hospital has the potential to improve the detection rate of respiratory viruses, improve the use of influenza antivirals and reduce unnecessary antibiotic use, but high quality randomised trials with clinically relevant endpoints are needed.

**Methods:**

The ResPOC study is a pragmatic randomised controlled trial of molecular point-of-care testing for respiratory viruses in adults with acute respiratory illness presenting to a large teaching hospital in the United Kingdom. Eligible participants are adults presenting with acute respiratory illness to the emergency department or the acute medicine unit. Participants are allocated 1:1 by internet-based randomisation service to either the intervention of a nose and throat swab analysed immediately on the FilmArray Respiratory Panel as a POCT or receive routine clinical care. The primary outcome is the proportion of patients treated with antibiotics. Secondary outcomes include turnaround time, virus detection, neuraminidase inhibitor use, length of hospital stay and side room use. Analysis of the primary outcome will be by intention-to-treat and all enrolled participants will be included in safety analysis.

**Discussion:**

Multiple novel molecular POCT platforms for infections including respiratory viruses have been developed and licensed in the last few years and many more are in development but the evidence base for clinical benefit above standard practice is minimal. This randomised controlled trial aims to close this evidence gap by generating high quality evidence for the clinical impact of molecular POCT for respiratory viruses in secondary care and to act as an exemplar for future studies of molecular POCT for infections. This study has the potential to change practice and improve patient care for patients presenting to hospital with acute respiratory illness.

**Trial registration:**

This study was registered with ISRCTN, number ISRCTN90211642, on 14th January 2015.

## Background

### Background and rationale

#### Respiratory virus burden of disease

Respiratory tract infections are the second most common cause of mortality and morbidity worldwide [1] and viruses are the most frequently detected pathogens in acute respiratory illness [2]. The influenza virus causes seasonal epidemics leading to excess hospitalisations and death mainly in the elderly and in patients with co-morbidity [3, 4]. Annual seasonal influenza vaccine is recommended in at risk groups [5–7] however vaccine coverage rate is sub-optimal [8, 9] and high quality evidence for significant protection in the elderly is lacking [10, 11].

The rate of hospitalisation in adults with influenza has been estimated at 5 to 20 per 100,000 overall [12, 13] and may be as high as 1,200 per 100,000 in those over 85 years old [4]. Hospitalisation and death result from the complications of influenza including pneumonia and exacerbation of underlying cardiopulmonary conditions [14]. In adult patients hospitalised with laboratory confirmed influenza, 10–30% are admitted to critical care units and 3–15% die in hospital [15–17] with outcomes being predicted by co-morbidity [17, 18]. Estimates of the burden of influenza virus infection in hospitalised adults have traditionally been based on the incidence of the influenza-like-illness syndrome (ILI, defined as fever of >38 °C and new respiratory symptoms) rather than on laboratory confirmed influenza. ILI has poor sensitivity (around 50%) and specificity (0–63%) for the diagnosis of influenza in hospitalised adults even during periods of peak activity [19–22]. Where estimates of disease burden are based on laboratory confirmed influenza, laboratory testing of patients is based on clinical suspicion of influenza and is generally targeted to patients with respiratory symptoms and fever. However, in addition to acute respiratory presentations, influenza may present as decompensated cardiovascular disease, collapse or diabetic emergencies [23, 24]. For this reason many hospitalised cases of influenza are likely to remain undiagnosed. A recent Canadian study estimated that only around one in 14 ED visits due to influenza virus infection were correctly attributed to influenza [25]. It is likely, therefore, that the burden of influenza and other respiratory viruses amongst hospitalised adults and its economic impact have been under-estimated. In addition to influenza viruses, other respiratory viruses including rhinovirus, respiratory syncytial virus, parainfluenza viruses, human metapneumovirus and coronaviruses, cause acute exacerbations of COPD and asthma as well as other acute respiratory presentations [2], which lead to large numbers of hospitalisations every year and significant burdens upon healthcare systems.

#### Conventional rapid diagnostic tests

Rapid diagnostic tests for influenza, and other respiratory viruses, based on antigen detection in nasal samples have been available for many years but have been diagnostically inaccurate in adults, where sensitivity is around 50% [26, 27]. The poor sensitivity of these antigen-based tests limits their clinical utility and their use has not been associated with a reduction in antibiotic prescribing in adults [28].

The current gold standard diagnostic test for respiratory viruses is laboratory performed polymerase chain reaction (PCR) which is highly sensitive and specific but has turnaround times of at least 24 h and requires specialist laboratory facilities and expertise [29]. New rapid, molecular tests have recently been developed, including the FilmArray Respiratory Panel. These molecular platforms are comparable in accuracy to laboratory PCR, without the need for specialist laboratory support and expertise, and can potentially be used as a point-of-care test (POCT), but the evidence for molecular POCT improving patient outcomes is weak.

#### FilmArray Respiratory Panel

The FilmArray Respiratory Panel (BioFire Diagnostics, Utah, USA, owned by bioMérieux) uses nested real-time PCR to detect 20 respiratory pathogens. The FilmArray requires only 2 min of “hands on” time and produces a test result in about one hour [30]. The FilmArray Respiratory Panel is both FDA-cleared and CE IVD marked. The viral pathogens detected by the FilmArray Respiratory Panel are: Influenza A (untyped, A/H1, A/H1-2009, A/H3), Influenza B, Adenovirus, Coronaviruses (HKU1, NL63, 229E, OC43) Human Metapneumovirus, Human Rhinovirus/Enterovirus, Parainfluenza (types 1, 2, 3, 4) and Respiratory Syncytial Virus. Three bacterial respiratory pathogens are also detected: *Bordetella pertussis*, *Chlamydophila pneumoniae* and *Mycoplasma pneumoniae* [30, 31].

The FilmArray respiratory panel is broadly equivalent in accuracy to laboratory PCR, and use has been validated on nose and throat swabs, nasopharyngeal aspirates, lower respiratory tract samples, and samples from immunocompromised patients [31–37]. Initial mediocre sensitivity for adenovirus detection has been greatly improved [38]. All of these studies show favourable outcomes with FilmArray system, including reliability, accuracy, ease of use and turnaround time although these studies were conducted in a laboratory rather at the point-of-care and a disproportionate number of these studies were conducted from samples from children rather than adults.

#### Potential clinical impact of point-of-care testing for respiratory viruses

In hospitalised adults with acute respiratory illness, viruses are the most commonly detectable pathogen, with bacterial detection being much less frequent, although antibiotic use is almost universal [2]. Antibiotic over-use is partly driven by clinical uncertainty as to the aetiology of the acute respiratory illness and so by early identification of viruses antibiotic use may be prevented.

A study examining clinical outcomes in children has shown that use of the FilmArray reduced the duration of antibiotic use, the length of inpatient stay, and the time in isolation [39]. However, this was not a randomised controlled trial but examined outcomes pre- and post-implementation. To our knowledge, there have been no randomised controlled trials of this system as a point-of-care test examining the potential clinical and health economic benefits. Although there are data to suggest clinical benefits (in terms of duration of hospital stay, number of investigations, and antibiotic use) for use of rapid diagnostic tests of influenza and other respiratory viruses in children [40–43], the clinical benefits and cost effectiveness of such a strategy in adults are unknown [44].

A Cochrane review evaluating the use of rapid antigen tests for acute respiratory illness in children in the emergency department concluded that there is currently insufficient evidence to support rapid viral to reduce antibiotic use in this setting. The authors suggest an adequately powered trial with antibiotic use as the primary outcome [45].

#### Point-of-care testing in the wider context

The Department of Health commissioned Carter report into UK pathology services noted the importance of developing clinically relevant point-of-care diagnostic tests to reduce turnaround times and improve patient pathways [46]. The UK Medicines and Healthcare products Regulatory Agency (MHRA) document ‘Management and Use of Point-of-Care Test Devices’ sets out the context in which POCT should be considered for use and provides guidelines for their successful and safe implementation [47]. The objectives of this study are in line with these documents and it aims to examine the initial phase of a POCT programme: establishing a clinical need for the test and evaluating potential clinical benefits.

#### Alignment with global research priorities

In addition to being focused on patient and healthcare organisation outcomes, this clinical research is strongly aligned with several global research priority initiatives including the World Health Organisation’s Battle against Respiratory Viruses (BRaVe) initiative [48] and the global report into antibiotic resistance [49]. The BRaVe initiative aims to catalyse multidisciplinary research on strategies to prevent and treat medically important respiratory virus infections with the goal of timely integration of research advances into public health practice. Priority areas identified include improving diagnostic tests for viral respiratory illness and improving the clinical management of patients with acute respiratory viral illness which are both addressed by this study.

### Study aims and objectives

This study aims to prospectively evaluate whether use of a molecular point-of-care diagnostic test will improve clinical outcomes compared to routine clinical care, in adult patients presenting to the secondary care with acute respiratory illness. The primary objective of the study is to evaluate the impact of POCT on antibiotic use. The secondary objectives include evaluating the impact of POCT on influenza antiviral use, side room facility use, duration of hospitalisation and the turnaround time of results compared with standard laboratory based PCR.

### Trial design

This is a pragmatic randomised controlled trial with parallel groups allocated 1:1 to the intervention (POCT) and control (routine clinical care) arms. The framework is superiority. The study protocol adheres to the SPIRIT statement [50].

## Methods

### Participants, interventions and outcomes

#### Study setting

This is a single centre study based in secondary care. All patients will be recruited from the Acute Medical Unit (AMU) and Emergency Department (ED) of Southampton General Hospital, University Hospital Southampton NHS Foundation Trust, Southampton, UK.

#### Eligibility criteria

##### Inclusion criteria

Aged 18 years or overHas the capacity to give informed, written consent and is able and willing to adhere to the study proceduresIs a patient in Southampton General Hospital’s AMU or EDCan be recruited to the studywithin a 24 h period of first triage by ED staff ORwithin a 24 h period of arrival on AMU (if admitted directly to AMU)
Has an acute respiratory illness* and/or fever >37.5 °CDuration of illness less than or equal to 7 days

*An episode of acute respiratory illness is defined as an acute pulmonary illness (including pneumonia, bronchitis and influenza-like illness) or an acute exacerbation of a chronic respiratory illness (including exacerbation of COPD, asthma or bronchiectasis).

Provisional or suspected clinical diagnoses of acute respiratory illnesses are made by an AMU or ED clinician.

##### Exclusion criteria

Patients not fulfilling inclusion criteriaA palliative approach being taken by the treating cliniciansPreviously included in this study and re-presenting within the last 30 days after hospital dischargeDeclines nasal/pharyngeal swabbing

Concurrent, prior or subsequent enrolment in an observational study is not necessarily an exclusion criterion; this is at the discretion of the chief investigator.

#### Interventions

##### For those randomised to the interventional arm

A nose and throat swab will be taken by a member of research staff (doctor or nurse) according to standard protocols. Combined nose and throat swabs have been described as an effective approach to maximise PCR sensitivity for a large number of respiratory viruses [51]. Swabs are placed directly into viral transport medium (Sigma Virocult®, MWE, UK). The sample is analysed on the FilmArray Respiratory Panel as per training delivered by the apparatus manufacturer. Test results are normally available in about an hour using the FilmArray Respiratory Panel. In the event of a run failure, the analysis run will be repeated using the same sample. The FilmArray machines are located in or near the patient-care areas (AMU and ED). The machines may be operated by a study doctor, research nurse or research technician. The results of the test will be documented in the patient’s case notes and in the event of a pathogen being detected, a doctor from the clinical team responsible for the patient will be directly informed. The participant will also be informed of the result on the same day.

##### For those randomised to the control group

These patients will be managed using routine clinical care, as per current practice in this large teaching hospital in the United Kingdom, which is a justifiable comparator. Respiratory virus testing using laboratory PCR will be at the discretion of the responsible clinical team.

##### For both groups

A subgroup of participants may be approached for venous blood sampling and additional nasal/throat swabs to be stored for further study including immunological testing and viral sequencing. All samples will be stored devoid of participant identifiable information to protect participant confidentiality.

#### Outcomes

##### Primary outcome

Proportion of patients treated with antibiotics, measured retrospectively from case notes for the entire duration of hospitalisation or at 30 days, whichever is shortest

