##### Secondary outcomes

Median duration of antibiotic use, daysProportion of patients receiving only a stat dose of antibioticsProportion of patients receiving <48 h antibioticsProportion of patients receiving intravenous antibioticsMedian duration of intravenous antibiotics, daysProportion of patients with influenza treated with influenza antiviralsProportion of influenza antiviral use occurring in patients with influenzaMedian time to influenza antiviral use, hoursMedian duration of influenza antivirals, daysMedian duration of hospital stay, daysProportion of patients admitted to a side room*Median duration of side room use, days*Median time to isolation or de-isolation, days*Median length of hospital stay, daysMedian turnaround time of respiratory viruses testing, hoursProportion of patients with viruses detectedProportionate mortality in hospital and at 30 days post randomisationProportion admitted to Intensive care or high dependency unitsProportion re-presenting to hospital within 30 daysProportion re-admitted to hospital within 30 daysProportion with prolonged in-patient stay

* A side room is a single-patient room; the use of which is a surrogate measure for isolation for the purpose of infection prevention and control.

Every attempt will be made to recruit patients and deliver the results of POCT prior to antibiotic use however it is understood due to the usual processes of care in hospital that on some occasions antibiotics will be have been administered before POCT is performed or before results are available to clinical teams. Therefore we plan to also undertake a *post hoc* analysis of only those patients where antibiotics were not administered prior to POCT results being available to clinicians.

In view of the deliberately broad inclusion criteria, heterogeneity of treatment effect among different clinical groups is anticipated and therefore subgroup analysis for the primary and certain key secondary outcome measures is planned based on clinical group. Results for antibiotic use (including any use, single dose, and use of less than 48 h duration), duration of antibiotics, admission and length of hospitalisation will be assessed separately for each clinical subgroup.

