#### Participant timeline

Patients are identified in the AMU and ED by research staff according to eligibility criteria and once written informed consent is obtained they are immediately randomised to the intervention or control group. Those randomised to the intervention group have a nose and throat swab performed immediately by a study doctor or research nurse and this is then tested on the FilmArray machine. Results are available after approximately 1 h and are immediately communicated to the clinical team. Clinical data is then collected retrospectively for both groups. There are no follow up visits for either group.

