#### Sample size

Sample size is based upon the primary outcome measure of proportion of patients treated with antibiotics. Previous studies have demonstrated that around 75% of patients hospitalised in the UK with acute respiratory illness are treated with antibiotics [2]. Two small studies in hospitalised adult patients with acute respiratory illness have demonstrated reductions in the proportion of patients treated with antibiotics of around 10–15% in those tested for respiratory viruses [44, 52]. To detect a reduction in antibiotic use from 75 to 65% with a power of 0.8 and significance level of 0.05, 326 patients would be required in each group. Allowing for withdrawals in up to 10% of patients we aim to recruit 360 patients to each group (720 patients in total).

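### The primary outcome counts antibiotics given before randomisation; these events cannot respond to the test, and the sample size states no allowance for them, so power is at risk

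*Protocol article*

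**What the plan says.** All references are to the Protocol article.

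- **Primary outcome:** the endpoint is defined as "Proportion of patients treated with antibiotics, measured retrospectively from case notes for the entire duration of hospitalisation or at 30 days, whichever is shortest". An end is fixed; a start at randomisation is not.
- **Inclusion criteria:** recruitment is allowed within "a 24 h period of first triage by ED staff", or within 24 h of reaching the AMU for direct admissions.
- **Participant timeline:** randomisation follows consent at once and the swab follows randomisation at once. "Results are available after approximately 1 h and are immediately communicated to the clinical team".
- **Secondary outcomes:** staff will try to deliver results before antibiotics are given, but the protocol accepts that "on some occasions antibiotics will be have been administered before POCT is performed or before results are available to clinical teams". Its response is an "analysis of only those patients where antibiotics were not administered prior to POCT results being available to clinicians", labelled post hoc although it is announced in advance. The same section lists duration of antibiotics, stat dose only, under 48 h of antibiotics and duration of intravenous antibiotics.
- **Sample size:** the control rate rests on the statement that "around 75% of patients hospitalised in the UK with acute respiratory illness are treated with antibiotics". The target is "To detect a reduction in antibiotic use from 75 to 65% with a power of 0.8 and significance level of 0.05", giving 326 per group, raised to 360 for withdrawals. Patients already treated are not mentioned.
- **Statistical methods:** the primary comparison is a chi-square test by intention-to-treat, followed by logistic regression with age, sex and other covariables.

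**The concern.** The outcome is any use, yes or no. A patient who has had one dose before randomisation is already a yes, and neither allocation nor a test result can change that. Such a dose is a baseline characteristic, yet it is scored as an outcome event.

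The Background section gives the mechanism as prevention: early identification of a virus means that antibiotics need not be given. A dose already given cannot be prevented. The more patients are treated early, the smaller the part of the endpoint through which the test can act, and a useful test could then give a null primary result.

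The restricted analysis does not clearly repair this. It selects on the time at which the POCT result became available. Control patients have no POCT result, so no matching control set is defined.

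**Working it through.** **Inputs from the document.** Control rate 0.75, intervention rate 0.65, power 0.80, significance level 0.05, 326 per group, 1:1 allocation. Sidedness is not stated; I take the test as two-sided.

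**Input not in the document.** f is the share of all randomised patients already treated when the result arrives. I vary it as an assumption.

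**Step 1: reproduce the plan's figure.** With unpooled variance,

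n = (1.960 + 0.842)² × (0.75×0.25 + 0.65×0.35) / 0.10² = 325.7, so 326 per group.

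This matches. The pooled form gives 329. Pooled power at 326 per group is 79.7%, at 324 (360 less 10%) 79.5%, and at 360 it is 83.5%.

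**Step 2: reading A, the planned relative effect reaches only untreated patients.** The planned relative reduction is 0.10/0.75 = 13.3%. The intervention rate becomes

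p₂ = f + (0.75 − f) × 0.65/0.75.

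Example, f = 10%: p₂ = 0.10 + 0.65 × 0.8667 = 0.663, a difference of 8.7 points. The pooled standard error under no difference is 0.0357 and the unpooled one is 0.0355. The power argument is (0.0867 − 1.960×0.0357)/0.0355 = 0.47, so power is 68%.

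**Step 3: reading B, 10 points is already the whole-population effect.** Power stays at 79.7%. The relative reduction needed among patients not treated early is 0.10/(0.75 − f).

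| Assumed f | A: difference (points) | A: power, 326 per group | A: evaluable n per group for 80% power | B: relative reduction needed in the rest |
|---|---|---|---|---|
| 0% | 10.0 | 79.7% | 329 | 13.3% |
| 5% | 9.3 | 74.3% | 375 | 14.3% |
| 10% | 8.7 | 68.2% | 433 | 15.4% |
| 20% | 7.3 | 54.4% | 596 | 18.2% |
| 30% | 6.0 | 40.0% | 878 | 22.2% |
| 40% | 4.7 | 26.6% | 1431 | 28.6% |

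If all 360 per group are evaluable, power under reading A is 72.5% at f = 10% and 58.6% at f = 20%.

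**The case against.** **A reader might infer that the trial does not have its stated 80% power.** The document does not support that. The arithmetic is right for 75% versus 65%. Both the 75% rate and the earlier reductions are given as overall proportions treated, so they may already include patients dosed early. No share is given either: the protocol speaks only of some occasions and promises efforts to test first. The 24 h limit is a maximum for eligibility, not a typical delay.

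**The planning effect is the low end of the cited 10–15% range.** Read as absolute points and put through reading A, a true 15-point effect (75% to 60%, a 20% relative reduction) gives power of 95% at f = 10%, 86% at f = 20% and 80% at f = 25%. So 10 points could be a 15-point effect diluted by 25% early dosing. The protocol does not say that it was meant this way.

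**A reader might also infer that only the restricted analysis can detect an effect in patients dosed early.** That goes too far. The duration, stat-dose and under-48 h outcomes can still respond after a first dose. The trial is not powered on them, however.

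**The choice is defensible as pragmatic.** Whole-stay use reflects real workflow, and doses before randomisation are balanced in expectation, so they do not bias the primary comparison towards benefit. This stands for delay after randomisation, which is part of the effect of a testing policy. It is weaker for doses before randomisation, which no allocation could influence.

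**Conclusion.** The point holds as a weakness of outcome definition with a conditional cost in power. The text itself establishes three things: doses before randomisation count as events, the protocol expects some early dosing, and the sample size section states no allowance for it. The effect is dilution towards no difference, not a spurious benefit.

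The size depends on two facts that the document does not give: the early-treated share, and whether the 10 points already include those patients. On the less favourable reading, even a 5% share takes power from about 80% to 74%, and a 20% share takes it to 54%. On the other reading power holds, but the test must do more in the patients it can still influence (18% rather than 13.3% relative reduction at a 20% share), and the sample size section does not argue that it can. A shortfall in power is a risk here, not a demonstrated failure.

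**What to change.** Before database lock, and without sight of results by arm:

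1. Define the primary outcome as antibiotics given after randomisation, up to the existing end of the window, on the same clock in both arms.
2. Record any dose before randomisation as a baseline variable, and stratify or adjust the primary comparison for it. The planned logistic regression can carry this.
3. Keep whole-stay use as a secondary outcome.
4. Replace the restricted analysis with a pre-specified subgroup of patients not dosed before randomisation, which can be identified in both arms.
5. State in the sample size section whether 75% to 65% includes early-treated patients, and show power across the arm-blind early-treated share.

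**Cost.** Dose times are needed from the electronic prescribing systems already named as a data source; no patients or procedures are added. All randomised patients stay in the analysis, so intention-to-treat is preserved. The downsides are real:

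- It is a documented amendment to the primary outcome of an open-label trial.
- The new outcome mixes starting antibiotics with continuing them.
- Doses in the hour or so between randomisation and result still count.
- The 75% and 65% planning rates no longer apply directly and must be restated, and the stated power is likely to look less favourable.

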### Assignment of interventions

#### Sequence generation, allocation concealment and implementation

Once an eligible patient has been screened, and given fully informed, written consent they will be enrolled and assigned a unique participant identification number consecutively. A study team member will then use a dedicated internet-based randomisation service (sealedenvelope.com, which uses random permuted blocks of varying sizes) to obtain a computer generated randomisation code for the patient which will assign them to either the intervention or control group. Research staff will implement the allocation sequence and assign the patients to the group based on the allocation code from sealedenvelope.com.

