#### Blinding

As this is a pragmatic trial of a diagnostic device no attempt at blinding trial participants, research staff or care providers will be made. Data analysts will be blinded to group allocation.

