### Data collection, management and analysis

#### Data collection methods

Clinical and demographic data will be collected at the time of enrolment by research staff from patient paper case notes and electronic medical records. Outcome data will be collected retrospectively by research staff from paper case notes, electronic medical records, electronic prescribing systems, and electronic radiological and laboratory results systems. Final clinical diagnosis will be based on clinical discharge coding and discharge summaries. All source data will be entered into a standardised paper case report form. Patients withdrawn from the study will have no further data collected. Missing data was minimal in the pilot study and is not expected to be a significant issue; the use of multiple imputation will be considered should missing data exceed 10% in the primary outcome.

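### Unblinded research staff are to abstract the primary outcome from case notes that carry the POCT result, and no record is named as decisive; the bias risk is probably modest but cheap to reduce

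*Protocol article*

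**What the plan says.** All references are to the protocol article.

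- **Source.** The Primary outcome section says the proportion treated with antibiotics is "measured retrospectively from case notes for the entire duration of hospitalisation or at 30 days, whichever is shortest". It names no other record.
- **Other sources.** Data collection methods is wider: "Outcome data will be collected retrospectively by research staff from paper case notes, electronic medical records, electronic prescribing systems", followed by radiology and laboratory results systems. It sets no order among them and does not say that the primary outcome is treated differently.
- **What the notes contain.** Under the interventional arm: "The results of the test will be documented in the patient’s case notes". Control patients have no POCT, so only intervention patients' notes can hold such an entry.
- **Who is blinded.** The Blinding section says "no attempt at blinding trial participants, research staff or care providers will be made". The only masked role is the analyst: "Data analysts will be blinded to group allocation".
- **Who does what.** On allocation: "Research staff will implement the allocation sequence and assign the patients to the group". On testing: "The machines may be operated by a study doctor, research nurse or research technician". Research staff also collect the outcomes, and the article does not separate these duties.
- **Checks.** Data management and Auditing provide for data to be evaluated for accuracy against source documents, the latter through sponsor monitoring under written procedures.

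**The concern.** The open design is justified in the Blinding section by the pragmatic nature of a device trial. That reason covers patients and treating clinicians, whose behaviour is what the test is meant to change. It does not cover a yes/no outcome that is read from records afterwards, which can be protected without touching care.

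As written, the person coding the outcome knows or can see the arm, and may see the virus result, in the document that decides the outcome. With several records available and no precedence, how hard one looks for a dose can differ by arm. The cases most exposed are brief ones. The secondary outcomes count single stat doses and courses under 48 h separately, and the same section expects some antibiotics to be given before the POCT result is available. A patient with one early dose counts as treated, and is the patient most easily missed in a search of one record only.

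Blinding the analysts does not help here, because it takes effect after the outcome has been entered on the case report form. What is at stake is the one outcome on which the trial is sized. If doses were missed more often in the POCT arm, the error would look like the hypothesised benefit.

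**Working it through.** **1. The plan's own figure.** Inputs from Sample size: 75% v 65%, power 0.8, significance level 0.05 (taken as two-sided, since sidedness is not stated), 326 per group.

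n = (1.960 + 0.842)² × (0.75×0.25 + 0.65×0.35) / 0.10² = 325.7, rounded up to 326.

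This reproduces the stated number (the pooled-variance formula gives 329). Nothing below changes the sample size.

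**2. Miss rates that differ by arm.** Assumptions, none of them in the documents: true antibiotic use is 75% in both arms, 326 per arm are analysed, every treated control patient is found, and a share m of treated POCT patients is coded as untreated. Then:

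- observed POCT proportion p₂ = 0.75 × (1 − m)
- false reduction d = 0.75 − p₂ = 0.75m
- mean proportion p̄ = (0.75 + p₂)/2
- SE₀ = √[2p̄(1 − p̄)/326]
- SE₁ = √[(0.75×0.25 + p₂(1 − p₂))/326]
- two-sided rejection rate = Φ[(d − 1.960·SE₀)/SE₁] + Φ[(−d − 1.960·SE₀)/SE₁]

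Worked for m = 3%: p₂ = 0.7275, d = 0.0225, SE₀ = 0.03441, SE₁ = 0.03440. The two terms are Φ(−1.307) = 0.0957 and Φ(−2.615) = 0.0045, together 0.100.

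| m | Treated POCT patients missed (0.75 × 326 × m) | False reduction, points | Type I error, formula | Type I error, exact enumeration of the uncorrected chi-square test |
|---|---|---|---|---|
| 0 | 0 | 0 | 5.0% | 5.0% |
| 2% | about 5 | 1.5 | 7.2% | 7.2% |
| 3% | about 7 | 2.25 | 10.0% | 10.0% |
| 4% | about 10 | 3.0 | 14.0% | 14.0% |

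Nearly all the excess lies in the favourable direction: by exact enumeration, false claims of a reduction go from 2.5% to 6.4%, 9.6% and 13.8%.

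**3. The same miss rate in both arms.** Under 75% v 65% with 326 per arm, power falls from 0.797 to 0.770 (2% missed), 0.730 (5%) or 0.663 (10%). When use is truly equal, an equal miss rate leaves the arms equal and creates no false reduction. Only a miss rate that depends on the arm inflates the type I error.

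**4. The sections side by side.** Primary outcome names one record; Data collection methods names several and ranks none. Read together, they do not say whether a dose found in the prescribing system but absent from the notes counts, or the reverse.

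**The case against.** The strongest case against has five parts.

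- **The outcome is objective.** Any antibiotic, yes or no, is a recorded fact. If every source listed in Data collection methods is read, a treated patient is miscoded only when each dose is overlooked in all of them. This stands, and is why the risk is called modest. It is weaker if the Primary outcome wording is followed literally and only the case notes decide.
- **There are checks.** Data management and Auditing compare data with source, and the statistician is independent of the study team. This stands too, though neither section says that the checking is done blind to arm.
- **The article is a condensed protocol.** Detailed abstraction rules may sit in the full document, and their absence would be no finding. The point here rests on what is stated: the source, the collectors and their blinding status, and two sections that differ on the source.
- **The miss rates are invented.** Correct. They show sensitivity and do not estimate anything. Even at 4%, the false reduction of 3 points is under a third of the 10-point target.
- **Changing the source does not blind the collectors.** Correct, because the same staff allocate and may test. The remedy therefore has to move the classification step to someone masked.

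A reader might also infer that electronic prescribing is an arm-free source that the plan overlooked. The documents do not support either half. No section describes what that system displays, and an influenza antiviral order, for example, could hint at the arm. The system is also already listed as a source of outcome data.

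**Conclusion.** The point holds in a limited form. The plan states an open ascertainment rule for its primary outcome: unblinded research staff, who also allocate and may run the test, read notes that show the result in one arm, and two sections leave unsettled which record decides. The treatment decision cannot be masked in this trial, but retrospective coding of it can be, at least in large part.

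The likely bias is modest. A type I error of about 7%, 10% or 14% follows only if 2%, 3% or 4% of treated patients are missed in the POCT arm alone, with true use of 75% in both arms and no correction by monitoring. A reader might take these figures as evidence that the trial's error rate is inflated; they are not, because the documents give no miss rate in either arm. The change is worth making because it is cheap and protects the outcome on which the trial is powered.

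**What to change.** Align Primary outcome and Data collection methods as follows.

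1. Define the primary outcome as at least one antibiotic dose recorded as given in the electronic prescribing record or, where that record does not cover an area, in the drug chart. Keep the existing time window.
2. Apply the same prespecified source order and one written drug list in both arms.
3. Extract the drug entries by study number, without arm or test-result fields.
4. Have the data analysts, whom the plan already blinds, classify each patient as yes or no from that extract.
5. Record the source used for each patient, so that use of the fallback can be compared between arms.

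The text should not describe electronic prescribing as arm-free. Before adopting the wording, the sponsor should confirm that the system records doses given and which areas it covers, including both recruitment areas (ED and AMU), since the article says neither.

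**Cost.** A wording change and a data export, with no extra assessor and no change to sample size or care. Paper charts must still be read where electronic coverage is incomplete, and masking of that reader may be only partial.
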